**5.2.4 Loan Approval**

Participants that complete loan registration, loan application, and deposited required savings will have their loans reviewed for approval. All group members must sign the loan application indicating they approve the business idea. Upon group approval of loan, the center chairman nominates another center member to visit the home of the loan applicant to ensure s/he has the physical collateral listed on the loan application. When these procedures are completed and confirmed, loans are approved for an initial loan of TSH 160,000 ($100 USD).

### 5.2.5 Weekly Loan Repayment Sessions

Participants will meet with a loan officer for mandatory weekly repayment sessions. At these sessions members are required to pay principal, interest, and provide a weekly savings deposit.

For a first loan of TSH 160,000, weekly repayments for the two loan terms are:

- 6 months: TSH 5,300 principal and interest + TSH 2,000 in savings = TSH 7,300 per week
- 9 months: TSH 7,300 principal and interest + TSH 2,000 in savings = TSH 9,300 per week

(Appendix B)

Repayment sessions will be led by a Loan Officer, and may contain occasional discussions or informational sessions on successful business skills. During each session group leaders will collect payments from all others in their group, and then present the collective money to the center leader. Repayments will be recorded by the Loan Officer, who will also transfer payments back to YOSEFO.

### 5.2.6 Ongoing Access to Credit

Ongoing access to incrementally larger loan amounts is a key feature of microfinance. After successfully completing a loan cycle, camp members will be eligible for successive loans at increasing amounts. Required minimum savings to receive the loan will also increase with successive loan. Amounts available for the first three loan cycles are:

- 1^st^ Loan: TSH 160,000 (5% savings required)
- 2^nd^ Loan: TSH 300,000 (12.5% savings required)
- 3^rd^ Loan: TSH 450,000 (25% savings required)

Funds from this project will cover the first three loan cycles for participating intervention camp members. Those seeking a fourth loan will be eligible to receive this and future loans from YOSEFO. Minimum deposited savings for loans 3 or greater will be 25% of loan amount. The sum of suggested weekly savings deposits (TSH 2,000) will be greater than the minimum deposit required, and can be applied to this requirement.

## 5.3 Camp Health Leadership Implementation

The second component of the intervention targets peer leaders within their camps as health promoters for behavior change. This intervention component builds on the fact that it is possible to identify peer nominated leaders within the camps who are respected and trusted by their peers. To implement this intervention component we will take the following steps:

### 5.3.1 Nomination Process

Twenty percent of the total number of members at each camp will be nominated in to a Health Leadership role (n = Camp members on roster x 0.20). Nomination will occur at each camp separately when at least 50% of camp roster members are present. After discussing attributes of leaders, each camp member in attendance will nominate confidentially up to 3 leaders in their camps with these qualities. Leaders identified will then be approached and asked if they are interested in being trained as peer leaders for their camp.

### 5.3.2 Training

Nominated camp health leaders will attend a one week training that focuses on building skills in effective communication and social influence. Health leaders will be trained in groups with a maximum of 40 individuals at one time. The same training manual used in the pilot intervention, with minor modification will be used in this trial. The training will provide camp leaders with knowledge and will address myths and misconceptions related to HIV transmission, condoms, violence, and multiple partnerships. (Appendix C)

### 5.3.3 Implementation of Strategies with Camps

Once trained, leaders will be asked to implement the communication and social influence strategies they learned within their camps. Leaders will record information about the number of times they engage in peer discussions about the issues discussed in training, the topics, the sex of their discussant, and any challenges encountered. See Process Evaluation in Section 7.8.

### 5.3.4 Booster Training Sessions

Follow-up training sessions for the leaders will occur at 6 month intervals after the intervention has launched. The sessions will enable leaders across camps to share experiences and continue to build their skills.

## 5.4 Control Condition

Half of camps randomly selected in to the study (n=30) will be assigned to the control condition. Camps in the control condition will receive an HIV prevention training to be administered after the 30 month follow-up data collection with the intervention group. The 2-3 hour session will focus on how HIV is transmitted,

# 6. STUDY PROCEDURES AND ADVERSE EVENTS

## 6.1 Overview

This study will use both quantitative and qualitative methods to assess the impact of the study. We will closely document the process of the intervention implementation in order to better understand successes and failures and to facilitate replication if efforts are effective.

The behavioral survey will be conducted using Computer-Assisted Personal Interview (CAPI) at baseline and follow-up sessions. Each round of surveys will be conducted with all eligible camp members selected in to the study. We will measure changes in gender norms and risky sexual behavior as well as other potential mediators of STI risk listed in the Objectives section of this document. STI tests will be administered with a subset of men at baseline and all men at the 30 month follow-up. We will measure relative prevalence among men in the intervention as compared to those in the control condition.

## 6.2 Pre-test Survey

Prior to launching the baseline survey we will pre-test all survey items and CAPI procedures with fifty camp members who have similar demographic characteristics to our target population but are not members of an intervention or control camp. The reasons for this pre-test is to assess length of the survey, check response distribution, assess item comprehension, and pilot data collection procedures.

## 6.3 Baseline Behavioral Survey

Eligible and consenting camp members in the 60 selected camps will participate in a survey assessing socio-demographics, outcome variables and mediating variables (Appendix D). The questionnaires will be administered using CAPI by trained interviewers who are not intervention facilitators. The interview will last approximately 60 minutes. Interviews will take place in a central location within each ward, interviewers split between the four wards. Participants who appear influenced by drugs will be asked to return for an interview the next day.

## 6.4 Baseline STI Assessment

Urine and blood specimens for diagnosis of STIs (NG, TV, CT) and HIV will be requested from a sample of half of sexually active men at baseline. Baseline testing is employed to compare base prevalence in the two conditions.

## 6.5 Follow-up Behavioral Assessments

At 12 months and 30 months a follow-up behavioral assessment will be conducted among eligible and consenting participants in order to assess outcome and mediating variables. We will use the same procedures described for the baseline assessment.

## 6.6 Follow-up STI Assessment

At 30 months urine and blood specimens will be collected from 100% of eligible and consenting men for STI testing (NG, TV, CT) and HIV.

## 6.7 Qualitative Assessment

We will conduct 3 focused qualitative studies during the study period with a sub-sample of eligible and consenting members of intervention camps. Each study will have a different focus pertaining to HIV, IPV, or microfinance experience. The purpose of these studies will be to inform ongoing intervention activities. The results may be used to inform the booster training for health leaders as well as the microfinance information session that the loan officers do during the repayment sessions.

## 6.8 Process Evaluation

Process evaluation measures will be collected in both the microfinance and health leadership components through the life of the intervention.

### 6.8.1 Intervention Training

To ensure integrity and consistency of the microfinance and health leadership trainings, we will measure dose of intervention delivered, dose received by participants, participant satisfaction, implementation fidelity, reach, and other contextual factors. These analyses will result in real-time suggestions to improve intervention implementation, as well as provide data to better connect effectiveness of implementation and study outcomes.

### 6.8.2 Microfinance Repayment Monitoring

We will collect data on participation and repayment success at each weekly repayment meeting for all participating camp members. Loan Officers will collect this data in an Access database at each session to enable review of individual success as well as to aggregate results by camp over time. We will produce camp-specific monthly reports that show: rate of participation in loan access; rate of meeting attendance; rate of loan installment repayment; total savings deposited; rate of loan repayment completion; rates of dropout and default; and reasons for dropout or default.

### 6.8.3 Camp Health Leaders Monitoring

Camp Health Leaders will be required to keep a log of conversations they have with camp members pertaining to HIV and Gender-Based Violence. Logs are intended to measure the number of conversations, the topics of conversation, and any challenges faced. Forms will be collected monthly and used to inform booster sessions. Urgent challenges reported by CHLs will be followed up more frequently with direct contact from study staff.

## 6.9 Language of Interviews

The predominant language in the study area is Kiswahili. All survey interviews will be conducted in Kiswahili, with selected answers recorded on CAPI tablets. The CAPI instrument is able to switch between Kiswahili and English, thus enabling questions and responses to be viewed in both languages. Qualitative interviews will be conducted in Kiswahili and will be recorded. Recorded interviews will be transcribed and translated into to English.

## 6.10 Quality Assurance

Responsibilities for data quality assurance will be shared with the site and UNC staff. The various data collected through the life of this study will be checked, cleaned, and stored appropriately after each wave of data collection (See Section 8). For the first objective – enumerate and characterize camps – the Tanzania field coordinator and data entry staff will be responsible for removing entries that are redundant or where 50% or more of data is missing for a specific camp. For camps selected in to the study the Research Coordinator will work with camp leaders to get up-to-date camp rosters and ensure enough members are eligible and willing to participate to make the camp eligible for study participation. Data shared between sites will be de-identified, encrypted and transferred as password protected files.

Behavioral and biological data collected via CAPI and biological specimens will have several quality check procedures implemented. A hard copy contact form for each participant will record the unique Participant Identification Number, records of each attempted contact made to the participant, and final data collection result. Identical records will be entered in to the CAPI device. Nurses will keep separate records of all individuals that completed the baseline and endpoint behavioral surveys as well as whether or not participants provided specimens for STI testing. All survey data collected on CAPI will be stored initially in locked files with the data manager in Delhi, India. Copies of survey data will be locked within CAPI devices themselves, accessible only with password provided by the data manager. Duplicating records of behavioral and biological data collection results on hard copy and CAPI serve as a data check to ensure all data collected is accounted for.

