
# 2. STUDY OBJECTIVES

## 2.1 Primary Aim 1

Enumerate and characterize camps where young men at risk for HIV acquisition and transmission socialize in four wards of Dar es Salaam.

## 2.2 Primary Aim 2

To determine whether men in camps randomized to receive a microfinance and health leadership intervention have a lower prevalence of sexually transmitted infections (NG, TV, CT), and report perpetrating less physical or sexual violence against female sexual partners as compared to men in camps not randomized to receive the intervention.

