#### 3.2.2.1. Community Informant Interviews

Brief, structured interviews will be conducted with community informants to identify the camps. The goal is to interview as many people as necessary within each ward until there is saturation in the venue lists. The PLACE method recommends interviewing 4 community informants per 1,000 people in catchment area to reach saturation of locations high in HIV risky behaviors. Since camps have already been decided to be the intervention locations, we have estimated that 2 community informants per 1,000 people will be sufficient to develop a saturated list of camps.

Prior to beginning interviews, study staff will inform local government officials as to the purpose and process of the study. Interviewers will then systematically proceed through each *mtaa* (similar to street) in all four wards to complete community informant interviews. Community members familiar with the area and at least 15 years old will be interviewed. Interviewers will approach people encountered in the *mtaa*, and if willing to be interviewed will record they type of community informant for each interview from a pre-developed list (i.e. street vendor, mechanic, security guard, student). Community Informants will then be asked to provide the names of all camps they know of in the area as well as directions to the camp. This phase of data collection is expected to be completed in 2 months.

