#### 3.2.2.2 Camp Verification Interviews

Using the list of camps generated during the Community Informant interviews, interviewers will verify the geographical location of camps in the four wards of this study and record camp characteristics using the Camp Verification form. Following directions provided in the Community Informant interviews, research staff will record whether or not they found the camp, refine directions if found, record physical characteristics of the camp, and record GPS coordinates to map and view relative location of camps. The interviewer will then seek a camp leader for the Camp Verification interview, and if not available, other camp members. Camp leaders willing to participate and at least 15 years old will be asked other specific characteristics of the camp such as years of operation, number of members, whether dues are required, activities at the camp, time and day when most busy, and general safety among others. The camp verification component will generate a pool of camps for selection in to the trial. This phase of data collection is expected to be completed in 2 months.

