### 4.1.2 Camp Recruitment and Screening

Camps will be identified through the PLACE-based community informant and camp verification interviews. Approximately 2 community informants per 1,000 person population in each of the four participating study wards will be recruited for interviews, or between 400 and 500 individuals. A list of potential camps in the four study wards, and directions to these camps will be developed through Community Informant interviews. All camps identified through Community Informant interviews will then be visited for Camp Verification interviews to confirm existence and current operation, record GPS coordinates, and record characteristics of the camp through interviews with camp leadership. Camps included in the sampling frame will be those confirmed to exist and be in operation, of which GPS coordinates were recorded, and for which at least half of the camp verification interview questions were completed.

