### 9.1.2 Aim 1 Sampling and Analytical Technique

Aim 1 is to enumerate and characterize camps where young men at risk for HIV acquisition and transmission socialize in Dar es Salaam using the PLACE methodology.

**Primary analysis.** A list of camps in the four wards within Dar es Salaam will be collected through Community Informant interviews. A minimum of 450 interviews will be conducted with individuals located in the four wards of focus in Dar es Salaam. Research assistants will systematically move through each *mtaa* (street) in the ward to cover sufficient geographical space in each ward. Research assistants will return to each camp mentioned by community informants to verify whether or not it exists; if found to exist, camp characteristics and GPS coordinates will be collected. Frequencies of camp characteristic categories will be analyzed with SAS SURVEYLOGISTIC version 9.2.

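### Section 6.10 applies a whole-record deletion rule to the camp enumeration of Primary Aim 1, so an existing camp with a sparse record can drop out of the count

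*Protocol*

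**What the plan says.** Section 2.1 gives Primary Aim 1 as "Enumerate and characterize camps where young men at risk for HIV acquisition and transmission socialize in four wards of Dar es Salaam". Section 3.2.2.1 shows that near-complete coverage is intended, since the planned number of informants "will be sufficient to develop a saturated list of camps".

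Section 3.2.2.2 describes the verification visit. At the site, "research staff will record whether or not they found the camp, refine directions if found, record physical characteristics of the camp, and record GPS coordinates". Only then does the interviewer "seek a camp leader for the Camp Verification interview, and if not available, other camp members".

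Section 4.1.2 builds the trial sampling frame from camps that exist, are operating, have GPS coordinates, and "for which at least half of the camp verification interview questions were completed".

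Section 6.10 sets the data-cleaning rule. It opens with "For the first objective – enumerate and characterize camps – the Tanzania field coordinator and data entry staff", who are "responsible for removing entries that are redundant or where 50% or more of data is missing for a specific camp".

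Section 9.1.2 gives the Aim 1 analysis. Staff return to each named camp to check whether it exists, and then collect characteristics and coordinates if it does. The planned output is: "Frequencies of camp characteristic categories will be analyzed with SAS SURVEYLOGISTIC version 9.2". This section contains no deletion step. No section says that a removed camp known to exist stays in the total, or that the number of removals is reported.

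**The concern.** A count of venues needs only evidence that each venue exists. How much is known about a venue matters for describing it, item by item, but should not decide whether it is counted. The rule in 6.10 ties the two together by removing the whole record. A camp that staff located and mapped can therefore vanish from the enumeration because most of its other fields are blank. Its location and physical features then leave the descriptive tables as well.

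A completeness filter is reasonable for the sampling frame, because a camp cannot be screened for trial eligibility without basic information. Section 4.1.2 already supplies that filter. Attaching a similar one to Aim 1 adds nothing to the trial and works against the enumeration. At stake are the total and the descriptive frequencies of one of the two primary aims.

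**Working it through.** The protocol gives no figure for this point, so there is nothing to reproduce. The check is a comparison of texts, followed by arithmetic for scale.

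**Texts side by side**

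- *Scope.* Section 6.10 names the first objective. Section 4.1.2 concerns the sampling frame only.
- *What must be present.* Section 6.10 refers to a camp's data. Section 4.1.2 refers to verification interview questions. The denominators may differ.
- *Boundary.* For a record exactly half complete, 4.1.2 keeps the camp and 6.10 removes it, provided both rules use the same denominator.
- *Existence.* Sections 3.2.2.2 and 9.1.2 both treat finding the camp as a step separate from obtaining its characteristics. A verified camp with a mostly blank record is therefore possible.

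**Size of the undercount**

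Let T be the number of camps that exist and f the share of them removed for missing data. If the total is taken from the cleaned file, the reported count is T × (1 − f), the undercount is T × f, and the relative undercount is f.

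The protocol does not give f; 0 to 20% is assumed here. For T, section 1.7 reports 73 camps in one ward in the earlier study. Applying that figure to four wards gives 4 × 73 = 292. This is an assumption for scale, not an estimate.

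| f (assumed) | Lost of 73 | Lost of 292 |
|---|---|---|
| 0 | 0 | 0 |
| 1% | 0.7 | 2.9 |
| 5% | 3.7 | 14.6 |
| 10% | 7.3 | 29.2 |
| 20% | 14.6 | 58.4 |

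**Shift in a characteristic**

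Let p_kept and p_del be the frequency of a characteristic among kept and deleted camps. The frequency over all existing camps is (1 − f) × p_kept + f × p_del. The reported value is p_kept, so the error is f × (p_kept − p_del). With an assumed difference of 10 to 30 percentage points:

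- f = 1%: 0.01 × 10 to 0.01 × 30 = 0.1 to 0.3 points
- f = 5%: 0.5 to 1.5 points
- f = 10%: 1 to 3 points
- f = 20%: 2 to 6 points

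If kept and deleted camps do not differ, this error is zero whatever f is.

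**The case against.** The strongest reply is that 6.10 describes ordinary database cleaning. Several informants can name the same camp, which explains the redundant entries. Section 3.2.2.2 says verification produces the pool for trial selection, and the next sentence of 6.10 moves on to the selected camps. On this reading, 6.10 and 4.1.2 state one frame-building rule twice, loosely worded. That is plausible as to intent, but it does not remove the problem. The sentence in 6.10 names the enumeration objective, the sampling frame has its own filter elsewhere, and nothing restores a removed camp to the count.

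Several stronger inferences are tempting, and the documents do not support them.

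- *Every camp that declines the interview is deleted.* Section 6.10 speaks of data, and the observations and coordinates taken on site may count towards it. Other members may also answer when no leader is available.
- *The aim promises a census.* Aim 1 does not say so; completeness is implied by the saturation target in 3.2.2.1.
- *The count is certainly too low.* That requires at least one existing camp to meet the rule and the total to come from the cleaned file. The protocol states neither.
- *The remaining camps are the safer ones.* This is conjecture. Safety is asked about at verification, and unsafe camps leave the sampling frame by a separate eligibility step in 4.1.3.
- *The on-site observations are lost for good.* Section 8.2.3 keeps the paper forms, so they can be recovered.
- *The trial result is biased.* The filter acts before camps are selected and randomised. It can affect which camps the trial represents, but not the comparison of arms.

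The boundary mismatch is also small, and it is a contradiction only if the two rules share a denominator.

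**Conclusion.** The point holds in conditional form. Section 6.10 attaches to a primary aim a deletion rule that can remove camps known to exist, although existence is established separately and the sampling frame has its own completeness condition.

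Two assumptions turn this into an undercount: some existing camp meets the rule, and the reported total comes from the cleaned file. The shortfall then equals the deleted share, and the characteristics describe only the better-documented camps. Because the protocol does not give the share, the real size cannot be computed, and the ranges above are illustrations only. The matter is worth correcting because it touches a primary aim and the correction is cheap. It has no bearing on the validity of the Aim 2 comparison.

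**What to change.** In section 6.10, limit deletion for Aim 1 to redundant entries. State that every camp found and operating enters the Aim 1 total, however complete its record. Report each characteristic on the camps with that item observed, together with the number of incomplete records.

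Keep the half-complete rule for the sampling frame only, in section 4.1.2, with one denominator and one wording for a record that is exactly half complete.

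The cost is about one sentence in 6.10 and, if needed, a word or two in 4.1.2. No new data are required: the verification visit already records what the count needs, and the paper forms are retained if entries have already been removed.
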